## Abstract

**Background:**

Kidney transplant recipients’ poor medication adherence and poor control of comorbidities, particularly hypertension, are risk factors for graft rejection, graft loss, and death. Few randomized controlled trials (RCTs) have been successful in improving sustained medication adherence and blood pressure control among kidney transplantation recipients. We provide rationale for an RCT evaluating a mobile health medical self-management system for kidney transplantation recipients called Smartphone Medication Adherence Saves Kidneys (SMASK).

**Objective:**

Our objective is to determine whether SMASK is efficacious in improving medication adherence and sustaining blood pressure control among kidney transplantation recipients with uncontrolled hypertension and poor medication adherence compared to an enhanced standard care.

**Methods:**

This two-arm, 6-month, phase II single-site efficacy RCT will involve 80 kidney transplantation recipients. Participants will be randomly assigned to the SMASK intervention arm or control arm. SMASK includes multilevel components: automated reminders from an electronic medication tray; tailored text messages and motivational feedback, guided by the self-determination theory; and automated summary reports for providers. Evaluations will be conducted preintervention, at 3 and 6 months, and posttrial at 12 months. Specific aims are to test the hypotheses that compared to standard care, the SMASK cohort will demonstrate significantly improved changes at 3, 6, and 12 months in the primary outcome variables medication adherence (proportion with electronic monitor-derived score >0.90) and blood pressure control (proportion meeting and sustaining adherence to the Kidney Disease Improving Global Outcomes [KDIGO] guidelines for blood pressure control); the secondary outcome variables provider adherence to KDIGO guidelines, measured by timing of medication changes and changes in self-determination theory constructs; and the exploratory outcome variables estimated glomerular filtration rate, variability in calcineurin inhibitor trough levels, and proportion of patients meeting and sustaining the 24-hour ambulatory blood pressure below 130/80 mm Hg. After the 6-month evaluation, interviews with a random sample of SMASK subjects (n=20) and health care providers (n=3-5) will assess user reactions including acceptability, usability, and aids/barriers to sustainability. Data from the RCT and interviews will be triangulated to further refine and optimize SMASK and prepare for a multisite effectiveness RCT.

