
This paper describes a 6-month efficacy RCT with a 6-month posttrial follow-up, utilizing a further refined SMASK mHealth system in kidney transplant recipients verified to be medication nonadherent with poorly controlled hypertension. The aims of this study are twofold: (1) to assess the efficacy of our mHealth system for monitoring and enhancing medication adherence and BP control during the 6-month active trial and the 6-month post-trial follow-up period and (2) to evaluate provider adherence to BP management guidelines and changes in participants’ levels of self-efficacy and autonomous motivation to sustain engagement in the medical regimen over time. Exploratory outcome variables will include changes in eGFR and variability of calcineurin inhibitor (CNI) trough levels (%cv).

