#### Exploratory Outcome Measures

These will include changes in estimated glomerular filtration rate (eGFR) and variability of CNI trough levels (%cv). CNIs have a well-described high inter- and intrapatient variability as well as a narrow therapeutic index. For these reasons, among others, therapeutic drug monitoring of CNI is the standard of care in solid organ transplantation and guides all CNI titrations [67,68]. Changes in the 24-hour ambulatory BP will also be examined.

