### Statistical Analyses

#### Primary Outcome Measures

The ITT analysis set will be determined in accordance with the International Conference on Harmonization E9 Guideline “Statistical Principles for Clinical Trials” [70] and will include all randomized subjects. For all subjects included in the ITT analysis set, all available data points will be included in the model. We chose a mixed-effects model approach because this method is a standard method in RCTs and can handle missing data and account for correlated data such as repeated measurements within patients or patients clustered within providers [71-73].

We propose a two-level analysis strategy: Our primary analysis will include the simple mixed-effects model containing the fixed time and intervention group, time, and time-by-intervention as primary independent variables (fixed effects) and MD as a random effect to account for clustering. The main analysis will compare the two intervention groups (SMASK vs SC) at the primary time point outcome at 3 months. We will estimate medication adherence score changes and changes in resting and 24-hour BP for each subject over the trial (preintervention and 1, 3, 6, and 12 months) and the within-subject longitudinal trajectories (eg, slopes) and summarize the mean longitudinal trajectory within each group. Intraclass correlations and variance estimates will be obtained for the efficacy outcomes and covariance structure of the longitudinal scores to determine the sample size (and hence adequate power) for a future effectiveness RCT.

In secondary/exploratory analysis for aim 1 outcomes, the potential influence of *a priori* specified covariates on these models will be explored, including self-determination theory tenants, demographic and clinical characteristics, and comorbidities. In an additional exploratory analysis, effect modifications of covariates will be examined through inclusion of covariate-by-group interaction terms in the multivariable models.

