#### Exploratory Outcomes Measures

In exploratory analyses, change in eGFR, variability of calcineurin trough levels, and 24-hour ambulatory BP will be compared between the two groups using pooled *t* tests (or nonparametric tests, as appropriate). If the end-of study outcomes for eGFR and 24-hour BP are missing, they will be imputed using multiple imputation methods. Further, frequency distributions of adverse events and serious adverse events will be determined, and proportions for the SMASK versus SC groups will be compared using Chi-square analyses.

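### The exploratory 24-hour ambulatory BP outcome is a sustained proportion below 130/80 mm Hg in the Abstract but a change in the body, and no stated analysis addresses the proportion

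*Protocol article*

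**What the plan says.** Four places in the protocol article describe the 24-hour ambulatory BP outcome.

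- **Abstract, Methods.** It is an exploratory outcome, worded as the "proportion of patients meeting and sustaining the 24-hour ambulatory blood pressure below 130/80 mm Hg". It sits in a sentence of hypotheses that "the SMASK cohort will demonstrate significantly improved changes at 3, 6, and 12 months".
- **Outcome Measures, Exploratory.** "Changes in the 24-hour ambulatory BP will also be examined". No threshold, proportion or persistence rule is given.
- **Statistical Analyses, Exploratory.** Together with change in eGFR and calcineurin inhibitor variability, "24-hour ambulatory BP will be compared between the two groups using pooled *t* tests", with nonparametric tests allowed where appropriate. On missing values: "If the end-of study outcomes for eGFR and 24-hour BP are missing, they will be imputed using multiple imputation methods".
- **Statistical Analyses, Primary.** "We will estimate medication adherence score changes and changes in resting and 24-hour BP for each subject over the trial", followed by within-subject trajectories and a summary of the mean trajectory in each group.

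Table 1 lists ambulatory BP as exploratory. By column position, it is recorded at baseline, 6 months and 12 months.

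**The concern.** A sustained proportion below 130/80 and a change in 24-hour BP are different outcomes. The first is binary, has a systolic and a diastolic limb, and requires persistence. The second is continuous, needs no threshold, and is not said to be systolic, diastolic or both. A between-arm difference in change does not show that more patients are below 130/80, or that they stay there.

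The article does name an analysis for 24-hour BP, so this is not a detail left to an unseen analysis plan. The named analysis belongs to the other definition. If the plan is followed, the Abstract's responder hypothesis gets no estimate and no test, and a later report could be faulted for departing from whichever definition it did not use. The article also does not say how the 24-hour BP description in the primary section relates to the comparison in the exploratory section.

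**Working it through.** The plan states no figure for this outcome. The only power statement, in Proposed Sample Size, covers the two primary proportions. The check is therefore a comparison of the text.

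**1. Form of the outcome**

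| Place | Form | Threshold | Persistence |
|---|---|---|---|
| Abstract | Proportion | 130/80 mm Hg | Yes, undefined |
| Outcome Measures, Exploratory | Change | None | None |
| Statistical Analyses, Exploratory | Continuous (t or nonparametric test) | None | None |
| Statistical Analyses, Primary | Per-subject change and trajectory | None | None |

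The threshold and the persistence requirement appear only in the Abstract.

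**2. Does any named analysis fit the proportion?** A pooled t test or a rank test on 24-hour BP, or on its change, does not estimate the share of patients below a threshold. The analysis sections name chi-square tests only for adverse events. The chi-square test in Proposed Sample Size refers to the two primary proportions, and the primary BP proportion uses clinic resting SBP. None is assigned to ambulatory BP.

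**3. Are the two outcomes interchangeable in this population?** No. Study Participants requires a 24-hour ambulatory SBP of at least 130 mm Hg after the monitoring period. If that recording is the baseline, nobody is below 130/80 at entry. A participant who starts well above 130 can fall substantially and still not meet the target. One who starts just above it can meet the systolic limb with a small fall. The diastolic limb adds a second condition that a systolic change says nothing about.

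**4. What could sustaining mean?** Table 1 gives two post-randomisation ambulatory recordings, at months 6 and 12. The only persistence rule these data can support is being below 130/80 at both. The month 12 recording falls 6 months after the active trial ends, so such a rule spans the post-trial period. The exploratory analysis refers to a missing end-of-study value, and a single value cannot show persistence.

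**5. Time points.** The Abstract's hypotheses run over months 3, 6 and 12. The primary section lists "changes in resting and 24-hour BP for each subject over the trial (preintervention and 1, 3, 6, and 12 months". Table 1 provides no ambulatory recording at months 1 or 3. Whichever definition is kept, only months 6 and 12 are available after randomisation.

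**6. How do the two statistical sections relate?** The primary section estimates per-subject changes and summarises trajectories within each group. The next sentence turns to variances and intraclass correlations for sizing a future trial. The exploratory section contains the only explicit between-arm comparison of 24-hour BP. The first is description and the second is a test, so they do not conflict. The article does not say which is the main result, and the description stands under the primary-outcome heading.

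**The case against.** The strongest defence has four parts.

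*The outcome is exploratory, and an abstract is a summary.* This stands as to size. It does not remove the mismatch: the Abstract is more specific than the body, giving a threshold, two limbs and persistence that the body never takes up.

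*The exploratory analysis need not be of change.* In the list that begins with change in eGFR, the word change may not govern ambulatory BP, and nonparametric tests are allowed. This is fair, and it means that a comparison of mean change is an inference. On either reading the variable is continuous and the proportion is not analysed.

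*The two statistical sections do not compete.* A reader might infer two incompatible analyses of one endpoint, with different status and different missing-data rules, and so room to report the more favourable one. The text does not support that. Only one between-arm comparison is stated. The Abstract, Outcome Measures, Table 1 and the exploratory analysis section all place ambulatory BP among the exploratory outcomes. The rule of using all available data is stated for the ITT analysis set and the primary model, and extending it to 24-hour BP is an inference. A mixed model on available data and multiple imputation are both accepted methods.

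*The Introduction omits ambulatory BP from its exploratory list.* That list says what the outcomes will include, so it need not be complete. I draw nothing from it.

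**Conclusion.** The point holds as an inconsistency of definition. The Abstract states a sustained proportion below 130/80, the body states changes and a test for a continuous variable, no stated analysis addresses the proportion, and sustaining is undefined for ambulatory BP. The placement of 24-hour BP trajectories under the primary heading needs a label and a ranking, but is not a contradiction.

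Severity is minor. The primary outcomes, their analysis and the sample size do not depend on this measure.

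A reader might want to express the mismatch as a loss of power for the proportion against the change. The documents do not support such a figure. They give no SD for 24-hour BP, no baseline-to-follow-up correlation and no expected effect, and the ranking of the two tests depends on those inputs and on how sustaining is defined. I therefore give none.

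The conclusion assumes that the columns of Table 1 were read correctly (baseline, 6 and 12 months) and that below 130/80 means both limbs.

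**What to change.** Use one definition in the Abstract, the exploratory outcome section and both statistical sections. Either route resolves the point.

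- **Change as the outcome.** Name change in 24-hour BP, stating systolic, diastolic or both, as the exploratory outcome. Compare arms in a baseline-adjusted model over the recordings at months 6 and 12, in place of the t test; the baseline value is already collected. Report the proportion below 130/80 at each of those visits as a supportive result with a confidence interval, and reword the Abstract to match.
- **Proportion as the outcome.** Keep the Abstract's wording, define sustaining as below 130/80 at both months 6 and 12, name a binary analysis, and state how a missing recording at either visit is handled.

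Under both routes, label the 24-hour BP trajectories in the primary section as exploratory and descriptive, say that the between-arm comparison is the main result for this measure, and limit its time points to those in Table 1.

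The cost is analysis wording, with no new data or visits. Under the first route the Abstract's responder statement becomes supportive. Results says that enrolment is complete and that only baseline data are being analysed so far, so on the article's account the definition can be fixed before outcome data are analysed. If that is no longer so, the choice should be dated and reported as made afterwards.

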**Results:**

The SMASK project received funding from National Institute of Diabetes and Digestive and Kidney Diseases in June 2016, obtained institutional review board approval in April 2016, and began data collection in July 2016. As of July 2018, we completed enrollment with a total of 80 participants.

**Conclusions:**

This study will provide data regarding the efficacy of SMASK to improve medication adherence and blood pressure control in a cohort of hypertensive kidney transplant recipients. An efficacious SMASK intervention will pave the way for a larger, multicenter, effectiveness RCT powered sufficiently to evaluate clinical events in a real-world setting and with the potential to demonstrate improved outcomes at lower cost than standard care.

**International Registered Report Identifier (IRRID):**

DERR1-10.2196/13351

## Introduction

End-stage renal disease (ESRD) affects more than 700,000 people living in the United States; of these, approximately 95,000 are currently awaiting kidney transplantation [1,2]. Kidney transplantation is the treatment of choice for eligible patients with ESRD, as it offers superior quality of life, improved life expectancy, and better psychosocial functioning, all at a lower cost than maintenance hemodialysis [3-6].

Advances in the medical and surgical care of transplant recipients have not resulted in optimal long-term graft survival. The current 5-year graft survival rate is only 78% [2], and the average graft half-life is only ~9 years [7]. Poor medication adherence and poor control of comorbid medical conditions, particularly hypertension, are major drivers of suboptimal kidney transplantation outcomes [8-13]. Nonadherence to prescribed medical regimens has been identified as a primary risk factor for graft rejection, graft loss, and death [14-18]. Even small degrees of nonadherence to immunosuppressant medications confer a significantly increased risk of graft rejection or graft loss [16,18]. In a meta-analysis published in 2007, approximately 35% of American kidney transplantation recipients demonstrated nonadherence to medications posttransplantion [19], with other more recent studies reporting values of 20%-40% [20-22].

Investigation on this topic has dramatically increased. A 2017 review of medication adherence intervention trials performed in solid organ transplant recipients identified 21 randomized controlled trials (RCTs), with 15 involving kidney transplant recipients. Two of the studies identified were our 3-month RCT [25] and the subsequent 12-month post trial follow-up study [27]. Intervention approaches in kidney transplant recipient studies varied widely and included cognitive behavioral therapy aimed at improving medication adherence [28,29]; psychoeducation [30]; intensified pharmaceutical care [31]; financial assistance programs [32]; electronic monitoring and reminders [33-35]; and our mHealth system that provides reminders, tracks medication taking, and delivers tailored motivational/social reinforcement messages based on the level of adherence.

Although approximately half of these RCTs involving kidney transplant recipients demonstrated a significant improvement in medication adherence, and the methodologies and measures of adherence varied widely. Most either did not examine drug blood levels or could not demonstrate an improvement in the examined levels related to medications(s) taken. None of the five RCTs in kidney transplant recipients that examined transplant outcomes (ie, estimated glomerular filtration rate [eGFR], graft rejection, graft survival, and serum creatinine) demonstrated significant improvement. None of these RCTs lasted >12 months, and the incidence rates of rejection and other relevant parameters were too infrequent to allow comparisons. Importantly, although poorly controlled hypertension is highly prevalent (70%-93%) [8,10,11] and a leading contributor to posttransplant reductions in kidney function, changes in associated physiological function (eg, BP) were not measured in any RCT except ours [26].

The authors concluded that research on medication adherence programs in the transplant population is misguided in that it often does not include patients verified as having poor medication adherence, lacks the use of programs that are engaging and foster sustained regimen adherence, and does not evaluate clinically relevant transplant-specific outcomes. Our work has addressed several of these issues including identification and recruitment of kidney transplant recipients with verified poor medication adherence using multiple indices. We chose to employ a two-part screening process including BP measurement and one-time medication adherence via medication possession ratio screening followed by a 1-month screening to determine medication nonadherence via a Bluetooth-enabled electronic pill box with audio and visual alerts disabled. In a pilot study, we found that 70% of otherwise eligible kidney transplant recipients were medication nonadherent [25], and thus far, we have identified a higher (~82%) proportion of such recipients in this RCT. Although medication nonadherence is on a continuum, it has been well demonstrated that even small degrees of medication nonadherence have negative effects on kidney transplant recipient outcomes [16-18]. We have employed a patient-centered, theory-guided, iterative design process to develop a medical regimen self-management program aimed at fostering self-efficacy and autonomous motivation to help ensure regimen adherence is sustained. In light of the expense and length of follow-up necessary to demonstrate significant clinical outcome improvements (eg, reduced acute rejection, graft loss, and death), we have adopted a strategy to investigate surrogate markers that are shown to be strongly predictive of worsened long-term outcomes (ie, BP and percent coefficient of variation [%cv]) [36-44]. A recent review of the literature on hypertension management in kidney transplant recipients concluded that posttransplant hypertension is prevalent (70%-90%), multifactorial, and rarely controlled (~33%) [8]. Specifically, among kidney transplant recipients at our transplant center, we found the prevalence of hypertension to be 95%, with only 34% having met the Kidney Disease Improving Global Outcomes (KDIGO) guidelines for hypertension control at a mean follow-up of 7.3 (SD 4.5) years after transplant [45]. Uncontrolled hypertension remains a significant problem in kidney transplant recipients; thus, efficacious intervention programs are warranted.

This paper describes a 6-month efficacy RCT with a 6-month posttrial follow-up, utilizing a further refined SMASK mHealth system in kidney transplant recipients verified to be medication nonadherent with poorly controlled hypertension. The aims of this study are twofold: (1) to assess the efficacy of our mHealth system for monitoring and enhancing medication adherence and BP control during the 6-month active trial and the 6-month post-trial follow-up period and (2) to evaluate provider adherence to BP management guidelines and changes in participants’ levels of self-efficacy and autonomous motivation to sustain engagement in the medical regimen over time. Exploratory outcome variables will include changes in eGFR and variability of calcineurin inhibitor (CNI) trough levels (%cv).

## Methods

### Trial Design

This is a two-arm, phase II efficacy RCT involving 80 kidney transplant recipients with poor medication adherence and uncontrolled hypertension, with subjects as the unit of randomization (ClinicalTrials.gov: NCT02827695). Each of the subjects was recruited and randomly assigned to the intervention or control arm by a statistician (who is not involved in subject recruitment or data collection) using a computer-generated random sequence. A flow chart of the study design is presented in Figure 1.

**Figure 1 figure1:**
[figure not shown]
SMASK clinical trial flowchart. SMASK: Smartphone Medication Adherence Saves Kidneys; SBP: systolic blood pressure; BP: blood pressure; SMS: short message service; KTR: kidney transplant recipient.

